This protocol has been developed in accordance with the Standard Protocol Items: Recommendations for Interventional Trials (SPIRIT) statement. A randomized two-arm clinical trial will be conducted (see Table 1; Additional file 1). Participants will be automatically randomized in a 1:1 ratio to one of two groups: an internet only (IO) control group or an internet plus motivational interview (IMI) group. Group randomization will employ computer-generated minimization using the program MINIM [24] and stratified by sex (male; female; other), gambling severity (low-moderate; high), and whether they have been previously treated for their gambling (yes; no) based on stratification strategies used in prior trials [12–14]. Gambling severity, for the purpose of randomization, will be defined based on PGSI scores of low-moderate (score of less than 8) or severe (score of 8 or greater). MINIM will generate the allocation sequence, which it conceals until the moment of assignment (i.e., participant stratification data is entered and MINIM returns the group assignment for each participant individually at the time of assignment).

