### Sample size estimation

The sample size was determined based on previous work exploring self-directed gambling interventions [11–14] and was computed using G*Power [36] on the basis of H1–H3. The estimation method was based on a repeated-measures between-factors ANOVA, which serves as a simpler derivative of the general linear model that the primary analyses will be based on [37, 38]. Two superiority hypotheses using three primary outcome measures will be analyzed using conventional two-tailed tests with thresholds of power = .80 and *α* = .05. Bonferroni corrections will be calculated to account for multiple comparisons. Correlations of *r* = .50 between baseline and follow-up data were accounted for [16]. A sample size of 108 participants per group will permit statistical detection of small effect sizes (Cohen’s *d* = 0.20 for continuous measures) at the specified significance level. This translates to differential detection of approximately 2 days less gambling per month and a 1-point decrease in NODS scores [37]. After accounting for 20% attrition over 12 months, the resulting planned sample size is 270 participants.

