### Data analyses

All statistical analyses will be conducted using SPSS version 26.0 at 12- and 24-month follow-up time points. Following completion of the 24-month follow-ups, the trial will be terminated. If baseline data are missing completely at random, they will be handled using the full imputation maximum likelihood approach to estimate means, variances, and covariances. Missing data at follow-ups will be handled with the multiple imputation method. Analyses will be conducted using the intention-to-treat (ITT) approach. Bivariate comparisons of all demographics and outcome measures will be conducted to explore differences between groups at baseline. Chi-square tests of independence will be used to compare groups on categorical measures, while *t* tests will be used to compare groups on continuous measures. Any primary outcome variables with significant differences between groups will be controlled for by entering them in as covariates in primary and secondary analyses. It is likely that the primary outcome variables will appear non-normally distributed when assessed with q-q plots and Shapiro-Wilk tests; in these cases, data will be appropriately transformed to achieve normality. If the data transformations are unsuccessful, separate nonparametric analyses will be conducted as appropriate instead of the respective planned analyses outlined below. Additionally, chi-square tests of independence will be used to determine if attrition rates differ in terms of treatment group or baseline characteristics.

H1 and H2 will be analyzed using generalized equation estimation (GEE) to determine if there are group (IO; IMI) differences in change over time. Outcome variables will include gambling frequency (i.e., number of days gambled in the last month), expenditures (i.e., average number of dollars lost per gambling day), and severity (i.e., NODS score). GEE is advantageous because it can account for the natural correlations over time in longitudinal data [38].

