To aid in clinical significance and translation, H1 and H2 will also be analyzed categorically with two separate logistic regressions. Both analyses will include Group and Time as binary predictors. The analysis to test H1 will include gambling disorder status (meets criteria; does not meet criteria) as the binary outcome. The analysis to test H2 will include recovery status (abstinence; improvement; no improvement) as the multinomial outcome. Improvement is defined as at least a 50% reduction in average number of dollars lost per gambling session.

H3 will be analyzed with a bivariate Pearson correlation between time spent on the site and change in dollars spent per gambling day from baseline to follow-ups.

H4 will be analyzed with two bivariate comparisons. Two unpaired *t* tests will be conducted to determine if the adherence rates differ by group after the 12- and 24-month follow-ups. Adherence will be measured in two ways: (1) number of modules completed on the program and (2) total time spent on the program website.

To test the exploratory research question, bivariate comparisons will be conducted. Q1 will be analyzed with an unpaired *t* test comparing group treatment ratings at each of the follow-up periods (3, 6, 12, and 24 months).

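### Baseline adjustment depends on a significance test, so the primary model is not fixed in advance and precision is probably lost

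*Protocol article*

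**What the plan says.** The Data analyses section of the protocol article announces baseline testing: "Bivariate comparisons of all demographics and outcome measures will be conducted to explore differences between groups at baseline". Chi-square and t tests are named for this purpose. The results then decide the model: "Any primary outcome variables with significant differences between groups will be controlled for by entering them in as covariates in primary and secondary analyses". No covariate is fixed in advance for any model.

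The main analysis of the three primary outcomes (gambling frequency, expenditures, NODS severity) is a GEE, used "to determine if there are group (IO; IMI) differences in change over time". The article does not list the time points that serve as responses, the full set of model terms or the working correlation. For the two supporting logistic regressions it says: "Both analyses will include Group and Time as binary predictors".

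Allocation is described under Participant validation: "Group randomization will employ computer-generated minimization using the program MINIM". The factors are sex, PGSI severity (below 8, or 8 and above) and previous gambling treatment. Sample size estimation assumes a correlation of .50 between baseline and follow-up, d = 0.20, 108 per group, and 20% attrition.

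**The concern.** When allocation is random, a baseline difference between arms is a chance event and a p-value for it answers no useful question. Whether a baseline value should be in the model depends on how well it predicts the outcome. The plan itself assumes that it predicts well (r = .50). The rule therefore uses the wrong criterion: it discards a prognostic covariate whenever the arms happen to look alike, and it leaves the primary model undetermined until the data are in.

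At stake are the precision of the primary comparison and having one pre-specified model per outcome. The rule also admits only primary outcome variables, so it can never bring in the three factors on which allocation was balanced.

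**Working it through.** **The plan's own figure.** 2 × 108 = 216, and 216 / 0.80 = 270, as stated. A figure close to 108 per group follows from a repeated-measures interaction test with f = 0.10, r = .50, three measurements and α = .05/3: N = 212, with power .811 at N = 216. The three measurements, the divisor of 3 and the choice of the interaction test are assumptions. Nothing below depends on them.

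**How often the gate opens.** Assume each baseline test uses .05. For three independent outcomes, P(at least one significant) = 1 − .95³ = .143. A single outcome's own baseline triggered in 4.4% to 5.1% of simulated trials. So in about 86% of trials or more no covariate enters at all.

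**Precision with one follow-up.** Take outcome variance 1 at each time and baseline–follow-up correlation r. The variance factors for the between-group contrast are:
- follow-up only: 1
- change from baseline, baseline means free in each arm: 2(1 − r)
- adjusted for baseline: 1 − r²

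| r | change | adjusted | reduction against change |
|---|---|---|---|
| .3 (assumed) | 1.40 | .91 | 35% |
| .5 (plan) | 1.00 | .75 | 25% |
| .7 (assumed) | .60 | .51 | 15% |

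At r = .50, 1/.75 = 1.33, so 108 per arm acts like 144. At this r the change contrast is no more precise than ignoring baseline.

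**In terms of power.** The detectable d at 80% power with 108 per arm, α = .05 and one follow-up is 2.80 × √(2/108) = 0.38 without adjustment, and 0.38 × √.75 = 0.33 with it. In simulation (normal data, r = .50), power at d = 0.38 was .89 with adjustment always made and .80 to .81 under the conditional rule.

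**Type I error.** Under the null, the conditional rule rejected in .043 to .044 of simulated trials, which is slightly conservative.

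**What happens when the gate opens.** If baseline is the first GEE response, the baseline covariate is constant within a participant. It can shift a participant's overall level but not the change over time. In simulated complete data (108 per arm, baseline plus four follow-ups, r = .50, independence and exchangeable working correlation), adding it left the group-by-time estimate and its standard error the same to five decimals. The correction is then inert in exactly the situation for which it was written.

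**Minimisation factors.** None of the three is a primary outcome variable, so the rule cannot admit them, and the article names none of them in any model. If a balanced factor explained an assumed 10% to 30% of outcome variance, leaving it out would lower type I error to .038 to .021. Power at d = 0.38 would be .80 to .84, against .83 to .92 with adjustment. The document does not say how prognostic the factors are, nor how much they add once the outcome's own baseline is in the model.

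**The case against.** The rule is written in advance, is mechanical and is confined to primary outcomes, so it leaves little room for discretion. That is fair: the model is data-dependent, but it is not chosen after the event at the analyst's will.

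The precision loss depends on a GEE that the article does not fully describe. If baseline means were constrained equal across arms, with a working correlation other than independence, baseline as a response would recover about the adjusted variance. This stands as a condition on the figures. The text does not describe such a constraint, and a rule that adds baseline covariates when the arms differ does not suggest one.

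Several stronger readings are tempting but are not supported:
- *That the rule inflates false positives.* It does not; the test becomes slightly conservative.
- *That the estimate is biased.* An imbalance just short of significance with 135 per arm is 1.96 × √(2/135) = 0.24 SD, and at r = .50 it moves the estimate by about 0.12 SD. That is the edge of the range. Over repeated randomisation the shift averages to zero, and the standard error already allows for it.
- *That the gate opens in 14% of trials.* This assumes independence. The article reports r = .50 between NODS and both days gambled and dollars spent, and minimising on PGSI severity makes a NODS imbalance less likely. The figure is nearer an upper limit.
- *That the plan excludes the minimisation factors from the GEE.* The article is silent on this, and a fuller plan could name them. What it does state is a rule that cannot admit them and logistic models that name only Group and Time.
- *That the trial is under-powered, which would make this worse.* That is a separate question, and this point does not rely on it.

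**Conclusion.** The point holds as one of efficiency and pre-specification. The gate is stated outright, so it is not a detail left to a fuller document. It makes the primary model depend on chance and in most trials leaves prognostic baselines out as covariates. If baseline is already a GEE response, as the stated interest in change over time suggests, it does little or nothing when triggered.

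At the plan's r = .50 and one follow-up, the cost is a variance of 1.00 where .75 was available. This assumes equal variances over time and baseline means not constrained equal. The validity of the test is not threatened. The gain from adding the minimisation factors cannot be quantified from the document.

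**What to change.** - Delete the significance gate and report baseline comparisons descriptively.
- For the between-group test of each primary outcome, and of each secondary outcome measured at baseline, use as responses the follow-ups available at that analysis: 3, 6 and 12 months for the first, with 24 months added for the second. Enter the outcome's baseline value as a covariate. Equivalently, fit a repeated-measures model with baseline means constrained equal and a working correlation other than independence.
- Include sex (with the category other collapsed if sparse), PGSI below 8 or 8 and above, and prior treatment as fixed covariates.
- For outcomes with no baseline value (modules completed, time on site, workbook ratings), adjust for the minimisation factors only.
- H1 to H3 also predict a reduction within each arm. Estimate these separately as change from baseline, because a model with follow-up responses only does not give them directly.

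The cost is a change of wording and one extra set of within-arm estimates. Every covariate is collected before randomisation, so no new data are needed.

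### The primary GEE depends on a normality check that GEE does not need; if transformation fails by an unstated criterion, an unnamed nonparametric analysis replaces it

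*Protocol article*

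**What the plan says.** The Data analyses section of the protocol article sets out a sequence of three steps.

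1. Check: "It is likely that the primary outcome variables will appear non-normally distributed when assessed with q-q plots and Shapiro-Wilk tests".
2. Transform: "in these cases, data will be appropriately transformed to achieve normality".
3. Replace: "If the data transformations are unsuccessful, separate nonparametric analyses will be conducted as appropriate instead of the respective planned analyses outlined below".

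The main planned analysis that follows is this one: "H1 and H2 will be analyzed using generalized equation estimation (GEE) to determine if there are group (IO; IMI) differences in change over time". It lists three outcomes. The first is a day count: "gambling frequency (i.e., number of days gambled in the last month". The second is a money amount: "expenditures (i.e., average number of dollars lost per gambling day". The third is a symptom score: "severity (i.e., NODS score". The sentence names two hypotheses, but all three primary outcomes are listed, so I read the GEE as primary for all three. The article's stated reason for the method concerns correlation, not distribution: "GEE is advantageous because it can account for the natural correlations over time in longitudinal data".

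The article names no transformation, no criterion for an unsuccessful one and no nonparametric method. The same section schedules analyses at 12 and 24 months. The sample size section expresses the target effects on the raw scale: about 2 gambling days a month and 1 NODS point.

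**The concern.** The replacement rule treats non-normal outcomes as a reason to abandon the GEE. GEE with robust standard errors rests on a correctly specified mean and on independent participants, not on normal data, so the rule guards against a problem the planned method does not have.

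It also has a cost. Whether the rule is triggered, and what replaces the GEE, would be settled with the outcome data in hand. The answer could differ between days, dollars and NODS, and between the 12- and 24-month analyses of the same outcome. A common fallback, a rank test at one visit, does not estimate the difference in change that the hypotheses describe, nor the raw-scale effects used for sizing.

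**Working it through.** **Inputs.** From the article: 108 evaluable per group, 20% attrition, N = 270, r = .50 between baseline and follow-up, and four follow-ups. Outcome shapes and zero shares are not in the article and are assumed. Zeros in days at follow-up are plausible because abstinence is one of the planned recovery categories. At entry, participants must have gambled in the last month.

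**The plan's own figure.** 2 × 108 = 216, and 216 / (1 − 0.20) = 270, as stated. It serves here only to set the simulated sample size.

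**Does GEE need normality?** With a separate mean for each group and visit and an independence working correlation, the group-by-time estimate is the mean change under IMI minus the mean change under IO. Its robust variance is s²(IMI)/108 + s²(IO)/108. Normality enters only through the distribution of means over 108 people. Simulated type I error with complete data, no true effect and nominal 0.05:

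| Assumed outcome | Test | Type I error |
|---|---|---|
| Log-normal dollars, 32% zeros at follow-up | 1 df / 4 df | 0.043 / 0.045 |
| Over-dispersed days capped at 30, 18% zeros | 1 df / 4 df | 0.058 / 0.060 |
| Same days, fitted GEE, Gaussian identity | 1 df | 0.045 |
| Same days, fitted GEE, Poisson log link | 1 df | 0.058 |

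The first two rows use 5,000 runs (Monte Carlo error √(0.05 × 0.95 / 5000) = 0.003), the last two 400 runs (√(0.05 × 0.95 / 400) = 0.011). The day-count results in the second row are slightly above nominal, but not by enough to justify abandoning the method. NODS was not simulated for type I error.

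**Would the check be failed after transformation?** Shapiro-Wilk rejection at 0.05, n = 216:

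| Outcome and scale | No zeros added | 5% zeros | 10–40% zeros |
|---|---|---|---|
| Dollars, log | 4% | 100% | 100% |
| Dollars, square root | 100% | 100% | 100% |
| Dollars, Box-Cox | 2% | 98% | 100% |
| Days, log | 100% | 100% | 100% |
| Days, square root | 100% | 99% | 100% |
| Integer 0–10 score, raw or square root | 100% | 100% | 100% |

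A monotone transformation sends tied values to one tied value, so it cannot remove a spike at zero or the steps of an integer score. The 0–10 range for severity is an assumption; the article says only that the NODS has 17 items.

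**What a single-visit fallback gives up.** Take unit variance and a correlation of .50 between all visits (the article gives .50 only for baseline with follow-up).

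- Mean of four follow-ups: (1 + 3 × 0.5) / 4 = 0.625.
- That mean minus baseline: 0.625 + 1 − 2 × 0.5 = 0.625.
- One visit, unadjusted: 1.0. One visit minus baseline: 1 + 1 − 2 × 0.5 = 1.0.
- Ratio: 1.0 / 0.625 = 1.6.
- At 12 months, with three follow-ups: (1 + 2 × 0.5) / 3 = 0.667. The change variance is 0.667 + 1 − 1 = 0.667, and the ratio is 1.5.

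These are variances of means, and so only a guide to the cost of dropping visits. On skewed data a rank test may recover some of the loss. Its null behaviour is not in question: a Mann-Whitney test at 12 months rejected in 4.8% (dollars) and 4.4% (days) of the same simulated null trials.

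**The case against.** Several stronger readings are tempting, and the article does not support them.

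- **The plan expects to lose its GEE.** It expects the raw outcomes to look non-normal. It does not say that transformation will fail, and replacement comes only after that.
- **Replacement is nearly certain.** This follows only if a Shapiro-Wilk rejection decides the matter. Q-q plots share the check and no threshold is set, so a lenient visual reading could keep the GEE. That discretion is nevertheless part of the problem.
- **All three outcomes are spiked at zero.** The article gives no zero shares. Dollars per gambling day are undefined, not zero, for someone with no gambling days. Without zeros, log-normal dollars usually pass. The case is firmest for days and NODS.
- **Rank methods cannot test differential change.** They can: a rank test on change scores does so, and rank-based analysis of covariance adjusts for baseline. The fair criticism is that the method is unnamed and that the usual single-visit test changes what is estimated.
- **The fallback inflates variance 2.7-fold.** That figure is 1 / 0.375, where 0.375 = 0.625 − 0.25 belongs to a baseline-adjusted analysis. The article adjusts for baseline outcomes only if the groups differ significantly, so 1.6 is the relevant comparison.

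Naming the transformation and the test may also be left to a statistical analysis plan not shown here. That stands for those details. It does not cover the replacement rule, which the article itself states as a substitution rather than a sensitivity analysis.

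**Conclusion.** The point holds in this form: the article lets a normality check with no stated failure criterion replace the primary GEE with an unnamed method, although robust GEE does not need normal outcomes. Under the assumed shapes, with complete data and 108 per group, robust GEE kept type I error between 0.043 and 0.060. Under a strict Shapiro-Wilk reading, days and NODS-like scores would almost always reach the replacement step. Dollars would reach it if abstainers are entered as zero, and usually would not if the data are log-normal without zeros. How likely replacement is in practice cannot be read from the article. What is at stake is a primary method chosen after seeing data, possibly different by outcome or analysis time, and loss of the group-by-time and raw-scale estimates if a single-visit rank test is used. This should be changed before analysis; it does not invalidate the design.

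**What to change.** Delete the rule that lets non-normality replace the planned analyses. State that GEE with participant-level robust standard errors is the primary analysis of days gambled, expenditure as the protocol defines it, and NODS in all cases, whatever the distribution looks like.

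Fix the link and family for each outcome in advance. An identity link keeps the effects on the scale used for sizing. For days, a count model with a log link is an option if marginal mean differences are reported with it. A family restricted to non-negative values would not suit expenditure if net winnings can occur, since the baseline and follow-up questions ask about money won as well as lost.

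Report transformed-outcome and rank-based analyses as sensitivity analyses that cannot replace the primary one.

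The cost is wording: the method, data and sample size do not change. One small downside is that raw-scale means of skewed dollar losses are sensitive to extreme values, which the sensitivity analyses would show.

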**Table 1 Tab1:**
[figure not shown]
Schedule of enrolment, interventions, and assessments

Participants will be invited via email to complete follow-up assessments at 3, 6, 12, and 24months after their enrolment in the study. They will not be dropped from the study unless they explicitly request to withdraw by contacting the research team as indicated in the consent form. Participants who drop out or require ancillary or post-trial care will be provided with local resources (e.g., contact information for crisis lines, emergency departments, family physicians, etc.) and encouraged to create a non-research account with the online program.

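### The supplementary logistic and multinomial models make no stated allowance for repeated records per participant, and the levels of Time and the test term are not fixed

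*Protocol article*

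**What the plan says.** In the protocol article, Data analyses, the continuous outcomes are analysed by GEE "to determine if there are group (IO; IMI) differences in change over time", with the reason that "GEE is advantageous because it can account for the natural correlations over time in longitudinal data". The section then adds that "H1 and H2 will also be analyzed categorically with two separate logistic regressions". On the predictors it says: "Both analyses will include Group and Time as binary predictors".

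The two outcomes differ in kind. For the first, "The analysis to test H1 will include gambling disorder status (meets criteria; does not meet criteria) as the binary outcome", which is a state that exists at every assessment. For the second, "The analysis to test H2 will include recovery status (abstinence; improvement; no improvement) as the multinomial outcome", and "Improvement is defined as at least a 50% reduction in average number of dollars lost per gambling session", which is a change from baseline.

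There are five assessment occasions: a baseline taken before randomisation (Blinding) and follow-ups at 3, 6, 12 and 24 months (Participant recruitment and randomization, at Table 1). Data analyses also says that analyses are run at 12 and 24 months. The article does not say which two occasions, or groups of occasions, make up the binary Time.

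**The concern.** A Time predictor in a model for disorder status means that each participant supplies more than one row. An ordinary logistic or multinomial regression treats those rows as independent. The article gives correlation over time as its reason for using GEE, then names a different method for the same participants' repeated outcomes and says nothing about correlation there.

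The hypotheses (H1 to H3) predict a larger reduction with the motivational interview. Which coefficient expresses that depends on whether baseline is one of the Time levels, and no test term is named.

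These models are included for clinical translation, and the Discussion presents the categorical analysis as a strength. Their odds ratios are therefore likely to be quoted. Leaving Time and the test term open also leaves a choice that could be made after the data are seen.

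**Working it through.** **Inputs from the article.** Two-sided alpha 0.05; 108 per group after attrition (216 / 0.80 = 270, which reproduces the planned total); a correlation of 0.50 between baseline and follow-up, given for the sample size only. No figure is given for these two models.

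**Assumptions.** The correlation of the binary outcome and all event rates below are assumed. A correlation of 0.50 on an underlying normal scale becomes about 0.33 between binary outcomes at 50% prevalence. Underlying values of 0.3 and 0.7 become about 0.19 and 0.49.

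**Reading A: Time is 12 versus 24 months (two rows per person).** Group varies between persons, so ignoring clustering understates its variance by the design effect DE = 1 + (T - 1) x rho. The actual type I error is 2 x [1 - Phi(1.96 / sqrt(DE))]. With T = 2:

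| Binary correlation | DE | Formula | Simulation, 108 per group |
|---|---|---|---|
| 0.19 | 1.19 | 0.072 | 0.066 |
| 0.33 | 1.33 | 0.089 | 0.091 |
| 0.49 | 1.49 | 0.108 | 0.102 |
| 0.50 | 1.50 | 0.110 | not run |

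Time and Group x Time are within-person contrasts, so the error goes the other way. The variance factor is 1 - rho. At rho = 0.5 the rejection rate is 2 x [1 - Phi(1.96 / sqrt(0.5))] = 0.006. In simulation, with two or five rows, uncorrected rejection was 0.006 to 0.026 for Time and 0.006 to 0.033 for Group x Time. With cluster-robust errors all three terms returned to 0.043 to 0.060.

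On this reading Group does carry the hypothesis. With disorder status assumed at 50% versus 35% at both times, the Group test has power 0.79 with robust errors (0.85 uncorrected). Group x Time rejects only 0.047 of the time, because it asks merely whether the effect differs between 12 and 24 months.

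**Reading B: Time is baseline versus follow-up.**

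- Recovery status is a reduction from baseline, so it has no value at baseline and the model cannot be fitted.
- For disorder status, a main-effects Group coefficient averages the follow-up effect with a baseline difference that is null by randomisation. Assume follow-up prevalence of 60% versus 45%. The follow-up log odds ratio is ln(0.45/0.55) - ln(0.60/0.40) = -0.20 - 0.41 = -0.61. Fitting Group + Time to the four expected proportions, with equal arms and the same baseline prevalence in both, gives a Group coefficient of -0.51, -0.44, -0.37 and -0.33 for baseline prevalences of 95%, 90%, 80% and 70%. A simulation gave -0.52, -0.46, -0.39 and -0.34. The dilution is roughly 15 to 45%.
- Group x Time is the term that tests a larger reduction. With 80% in both arms at baseline and 50% versus 30% at follow-up (underlying correlation 0.5), its power is 0.61 with robust errors and 0.50 uncorrected. The main-effects Group term has 0.54 with robust errors.

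Neither reading suits both models as written. A leaves the Group standard error too small, and B makes one model impossible and the other's Group term the wrong test.

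**The case against.** The strongest reply is that this is silence in a condensed article. The sentence does not say that these are the only terms, and it excludes neither an interaction nor a clustered fit. It follows directly on a paragraph that recognises correlation over time and sets group differences in change as the aim. The 12- and 24-month analysis points supply a coherent two-level Time, under which Group is a valid randomised comparison. Recovery status is already a change, so Group alone tests differential improvement there.

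Much of this stands. A reader might infer that the plan rules out clustering and an interaction, that all p-values from these models are too small, or that the models do not test the hypothesis. The article supports none of these in general. The first rests on silence. The second is true only of the Group term and is reversed for Time and Group x Time. The third applies only to disorder status with baseline as a Time level.

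What does not stand is that nothing needs changing. The article names a model and its predictors and ties correlation handling to the GEE alone. Followed as written, the Group test is anti-conservative under Reading A.

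**Conclusion.** The point holds as a defect in two supplementary models. With two follow-up rows per person, the Group test runs at about 7 to 11% instead of 5%, for assumed binary correlations of about 0.2 to 0.5. With baseline as a Time level, the recovery model cannot be fitted. The disorder-status Group effect is then diluted, by roughly 15 to 45% under assumed prevalences that are not in the article, and the uncorrected Group x Time test is conservative.

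One might quote a type I error above 20%. That needs four follow-up rows pooled per person and a correlation near 0.5 (DE = 1 + 3 x 0.5 = 2.5, giving 0.215), which the article does not state.

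Nor does this undermine the trial's main conclusions: the GEEs are the main tests, and the sample size does not rest on these models. It should be fixed before analysis, at moderate priority.

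**What to change.** Amend Data analyses, or settle it in the analysis plan, in three respects:

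1. **Clustering.** Fit both models with participant as the cluster and robust standard errors: GEE with a logit link for disorder status, and a cluster-robust multinomial logit for recovery status.
2. **Time.** State its levels for each model. Recovery status can use follow-ups only.
3. **Test term.** For disorder status, name Group x Time if baseline is included. For any follow-up-only model, including recovery status, name Group, or the group contrast at one follow-up stated in advance (12 or 24 months; the article does not name a primary one). Do not make Group x Time the test in a follow-up-only model, because it would miss a constant effect.

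The cost is a change of wording, slightly wider intervals for the Group effect and a little more output. No data collection changes, and GEE is already planned. The team should confirm that the chosen SPSS procedure fits a clustered multinomial model; this was not checked here.
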